## Abstract

**Introduction:**

Same‐day discharge after primary total hip arthroplasty (THA) and total knee arthroplasty (TKA) is increasing, but the optimal anaesthetic technique for outpatient pathways remains uncertain. Neuraxial anaesthesia is widely recommended based on observational evidence, whereas fast‐track programmes using short‐acting total intravenous anaesthesia may facilitate early mobilisation and discharge. No randomised controlled trial has compared general anaesthesia (GA) with spinal anaesthesia (SA) specifically in outpatient primary THA/TKA using a same‐day discharge target.

**Methods and Analysis:**

GASPS is a pragmatic, multicentre, parallel‐group superiority randomised controlled trial. Adults scheduled for outpatient primary THA or TKA will be randomised 1:1 to GA or SA, with stratification by site and procedure (THA/TKA). The primary outcome is successful same‐day discharge (discharge on the day of surgery) without readmission within 48 h after discharge. The five key secondary outcomes are time to fulfilment of hospital discharge indicators, quality‐of‐recovery (QoR‐15) trajectories over postoperative Days 1–35, patients' qualitative experiences of anaesthesia and recovery, cost per quality‐adjusted life‐year and safety (adverse events); all remaining outcomes—including pain, postoperative nausea and vomiting, opioid consumption, mobilisation and patient‐reported outcomes (EQ‐5D‐5L and HOOS/KOOS)—are exploratory. An embedded qualitative study will explore patient experiences using semi‐structured interviews, and an economic evaluation will compare costs and outcomes from healthcare and societal perspectives. Analyses will follow the intention‐to‐treat principle; a group sequential design with O'Brien‐Fleming boundaries is planned for an interim analysis. Approval has been obtained from the Swedish Medical Products Agency. Written informed consent will be obtained from all participants. Results will be disseminated through peer‐reviewed publications, conference presentations and reporting in the EU Clinical Trials Information System (CTIS).

**Conclusion:**

This study is designed to determine the most effective anaesthetic method for same‐day discharge after primary TKA and THA. With increasing outpatient surgeries, this study will be helpful for optimisation of outpatient processes.

**Trial Registration:**

EU CT/CTIS: 2024‐520127‐89‐00. ClinicalTrials.gov: NCT07334132

AbbreviationsAEadverse eventASAAmerican Society of AnesthesiologistsAxMPauxiliary medicinal productBMIbody mass indexCTISclinical trials information systemEQ‐5D‐5Leuropean quality of life 5 dimensions 5 level versionEU CTeuropean union clinical trialGAgeneral anaesthesiaGASPSgeneral anaesthesia versus spinal anaesthesia for success in outpatient primary total hip and knee arthroplastyGCPgood clinical practiceGDPRGeneral Data Protection RegulationHEAPhealth economic analysis planHOOShip disability and osteoarthritis outcome scoreICERincremental cost‐effectiveness ratioKOOSknee injury and osteoarthritis outcome scoreNRSnumeric rating scaleNSAIDnon‐steroidal anti‐inflammatory drugOMEoral morphine equivalentsPACUpost‐anaesthesia care unitPODpostoperative dayPONVpostoperative nausea and vomitingQALYquality‐adjusted life yearQoR‐15quality of recovery‐15RCTrandomised controlled trialSAspinal anaesthesiaSAEserious adverse eventSAPStatistical Analysis PlanSPIRITstandard protocol items: recommendations for interventional trialsTHAtotal hip arthroplastyTIVAtotal intravenous anaesthesiaTKAtotal knee arthroplasty

## Introduction

1

### Background and Rationale

1.1

Primary total hip arthroplasty (THA) and total knee arthroplasty (TKA) are common and effective treatments for osteoarthritis and other degenerative or inflammatory joint diseases, leading to decreased pain, enhanced quality of life and reduced mortality [1, 2, 3]. Outpatient arthroplasty pathways can reduce costs and may reduce healthcare‐associated infection risk, with comparable patient satisfaction and, in selected patients, low complication rates [4, 5, 6]. Same‐day arthroplasty pathways are designed in accordance with Enhanced Recovery After Surgery (ERAS) principles, encompassing preoperative optimisation, opioid‐sparing multimodal analgesia, standardised antiemetic prophylaxis and early mobilisation [7]. However, unsuccessful same‐day discharge and unplanned readmissions remain important safety and implementation challenges [8].

Both spinal anaesthesia (SA) and general anaesthesia (GA) are routinely used for THA/TKA [9]. International consensus statements and observational comparative‐effectiveness research suggest neuraxial techniques may be associated with fewer complications and a higher likelihood of earlier discharge [10, 11, 12]. Conversely, fast‐track pathways using short‐acting total intravenous GA (TIVA) may facilitate earlier mobilisation and shorter length of stay in some contexts [13, 14]. Existing evidence in the outpatient setting is mixed and is largely observational, with potential confounding by patient selection (e.g., higher American Society of Anesthesiologists (ASA) classification among patients receiving GA in routine care) [15, 16].

There is a clear evidence gap regarding the comparative effectiveness of GA versus SA in outpatient primary THA/TKA when the primary goal is successful same‐day discharge and when recovery is assessed using validated patient‐reported recovery instruments.

### Objectives

1.2

#### Primary Objective

1.2.1

Evaluate the effect of SA versus GA on successful same‐day discharge in primary THA/TKA.

#### Key Secondary Objectives

1.2.2

Evaluate the effect of SA versus GA on early and intermediate recovery.Evaluate the effect of SA versus GA on late and long‐term recovery.Describe patient experiences of anaesthesia and postoperative care when undergoing outpatient primary TKA or THA.Evaluate the cost‐effectiveness of SA compared to GA from healthcare and societal perspectives.Assess the safety of SA and GA.

#### Exploratory Secondary Objectives

1.2.3

Evaluate the effect of SA versus GA anaesthesia induction (pre‐recovery) [17].Evaluate the effect of SA versus GA on pain and PONV.Evaluate the effect of SA versus GA on intraoperative parameters.

An observational cohort of screened patients ineligible for randomisation will be enrolled to allow descriptive analyses and exploratory comparisons with the randomised population.

## Methods and Analysis

2

### Protocol Reporting

2.1

This protocol is reported in accordance with the SPIRIT (Standard Protocol Items: Recommendations for Interventional Trials) guidance. A detailed Statistical Analysis Plan (SAP) and Health Economic Analysis Plan (HEAP) will be finalised and made available prior to database lock.

### Roles and Responsibilities

2.2

The sponsor of the trial is Region Örebro County. The sponsor is responsible for the overall study design, regulatory approvals, trial conduct, data management and reporting.

The principal investigators are responsible for the day‐to‐day conduct of the trial, including participant recruitment, data collection and adherence to the protocol at participating sites.

Trial oversight will be ensured through risk‐based monitoring performed by an independent monitor in accordance with Good Clinical Practice (GCP). No independent data monitoring committee is considered necessary since interventions are standard of care.

### Study Design

2.3

GASPS is a pragmatic, multicentre, parallel‐group superiority randomised controlled trial with 1:1 allocation to GA or SA. Randomisation will be stratified by site and type of surgery (THA vs. TKA) using permuted blocks. An observational cohort will enrol screened patients who are eligible for outpatient surgery but are not randomised because they decline one of the anaesthetic methods or are deemed unsuitable for either technique; analyses of the observational cohort will be descriptive and exploratory.

### Study Setting

2.4

Participants will be recruited from specialised orthopaedic surgical units in Sweden with established outpatient THA and/or TKA pathways.

### Eligibility Criteria

2.5

Inclusion and exclusion criteria are summarised in Table 1.

**TABLE 1 aas70283-tbl-0001:** Key eligibility criteria.

Inclusion criteria	Exclusion criteria
Written informed consent	Indication other than degenerative/inflammatory joint disease (e.g., fracture)
Scheduled for primary THA or TKA for degenerative or inflammatory joint disease	BMI > 35 kg/m^2^
Age 18–80 years at consent	Preoperative opioid use > 20 mg oral morphine equivalents/day
ASA physical status 1–2, or 3 without significant functional impairment	Haemoglobin < 120 g/L
Scheduled surgery start before 13:00 h.	Known bleeding disorder/coagulopathy
Able to communicate in Swedish	Allergy to study‐relevant anaesthetic drugs
	Neurological condition with persistent motor/sensory deficit
	Local infection at spinal injection site
	Determined unsuitable for outpatient surgery and/or trial participation by surgical/anaesthetic team
	Women of childbearing potential not willing to use highly effective contraception or with positive pregnancy test at enrolment
	Unwilling or unable to receive either GA or SA
	Participation in another investigational medicinal product trial within 30 days
	Previous participation in GASPS

### Recruitment and Consent

2.6

Potentially eligible patients will be identified through routine outpatient arthroplasty scheduling. Written study information will be sent to potentially eligible patients by post ahead of the preoperative anaesthesia assessment, at which the trial will be discussed in person. Participants will provide written informed consent prior to randomisation.

### Randomisation and Allocation Concealment

2.7

Participants will be randomised 1:1 to GA or SA on the day of surgery via a secure electronic case report form system. Randomisation will use stratified permuted blocks with stratification by site and procedure (THA/TKA) to balance allocation over time. Allocation will be concealed until assignment. Participants will not be informed of allocation until first contact with anaesthesia staff on the day of surgery to reduce expectation effects.

### Blinding

2.8

Blinding of anaesthesia clinicians and participants is not feasible. Most outcomes are objective time‐based measures (e.g., discharge milestones), recorded in routine care or patient‐reported, minimising but not removing the risk of bias. Data analysis will be performed blinded to treatment assignment until primary analyses are finalised.

### Interventions

2.9

#### General Anaesthesia Group

2.9.1

GA will be delivered as TIVA with propofol and remifentanil using target‐controlled infusion or rate‐controlled infusion according to local routine. Airway management will use a supraglottic airway device or endotracheal intubation according to clinical judgement and local practice.

#### Spinal Anaesthesia Group

2.9.2

SA will be delivered with intrathecal bupivacaine 0.5% (1.0–2.0 mL) and may be combined with intrathecal opioid (up to fentanyl 50 μg or sufentanil 10 μg) according to local routine. Light propofol sedation is permitted at the discretion of the anaesthesiologist. The dose range reflects current Swedish practice and accounts for patient characteristics (height, weight, age) and anticipated surgical duration [18, 19].

#### Co‐Interventions and Perioperative Care

2.9.3

Perioperative surgical techniques and perioperative care follow established ERAS principles for THA/TKA [7]. The standardised pathway across all sites includes: preoperative patient education, opioid‐sparing multimodal analgesia (paracetamol, NSAID when appropriate, and dexamethasone), standardised PONV prophylaxis, tranexamic acid, antibiotic prophylaxis and protocolised early mobilisation on the day of surgery. Site‐level variation in specific agents or doses is permitted within this framework, consistent with the pragmatic design. Conversions between anaesthetic techniques (e.g., failed spinal requiring GA) will be permitted as clinically necessary and documented.

### Outcomes

2.10

#### Primary Outcome

2.10.1

Successful same‐day discharge, defined as discharge from hospital on the day of surgery AND no readmission within 48 h after discharge.

#### Key and Exploratory Secondary Outcomes

2.10.2

The key secondary outcomes are (1) time from start of surgery to when the patient fulfils indicators of hospital discharge (criteria specified in Table 3), (2) Quality of Recovery (QoR) trajectories, (3) patients' qualitative descriptions of anaesthesia and postoperative recovery, (4) cost per gained quality‐adjusted life‐year (QALY) and (5) safety (adverse events). All other outcomes listed in Table 2 are exploratory, and no multiplicity correction is applied to them. Health economic data will be gathered to capture costs and QALY over a full year to account for seasonal variation, allow short‐term postoperative differences to resolve [20], and support annualised cost‐effectiveness estimates.

**TABLE 2 aas70283-tbl-0002:** Key and exploratory secondary outcomes.

Objectives	Outcomes	Assessment(s)
Key secondary outcomes		
*Evaluate the effect of SA* vs. *GA on early and intermediate recovery*	*Time from start of surgery to when patient fulfils indicators of hospital discharge (criteria specified in* Table 3 *)*	Performed by the discharging orthopaedic surgeon and/or nurse and registered as the time when indicators are fulfilled
*Evaluate the effect of SA* vs. *GA on late postoperative recovery*	*Quality of Recovery (QoR) trajectories*	QoR‐15 at baseline and daily postoperative Day 1–14 and once a week until postoperative day (POD) 35
*Describe patient experiences of anaesthesia and postoperative care*	*Patient's qualitative descriptions of anaesthesia and postoperative recovery*	Semi‐structured interviews with 20–30 participants 14–60 days after surgery
*Evaluate the cost‐effectiveness of SA* vs. *GA*	*Cost per gained quality‐adjusted life‐year (QALY), SA vs. GA*	Quality of life (EQ‐5D‐5L, HOOS/KOOS): questionnaires at baseline, 4 weeks, 6 and 12 months Intervention costs: time, material and personnel across stages of anaesthesia Healthcare consumption (inpatient, outpatient, primary care): administrative data, first year Prescribed medication: administrative data and medical records, first year Productivity and informal care: patient questionnaires at baseline, 4 weeks, 6 and 12 months
*Assess the safety of SA and GA*	*Adverse events (AE) and Serious AE (SAE)*	Reported by study staff (see Safety section), from start of anaesthesia to 3 days post‐surgery
Exploratory secondary outcomes		
Preoperative care and anaesthesia		
Evaluate the effect of SA vs. GA on anaesthesia induction (early recovery)	Time from start of anaesthesia to start of surgery	Times recorded by the anaesthesia or study staff
Postoperative recovery		
Evaluate the effect of SA vs. GA on early and intermediate recovery	Time from start of surgery to discharge from PACU (criteria specified in Table 3)	Assessed by the postoperative recovery unit nurse and recorded as the time of discharge
	Time from the start of surgery to hospital discharge	Assessed by the discharging orthopaedic surgeon and/or nurse and recorded as the time of discharge
	Time from start of surgery to first successful mobilisation by walking with tolerable pain	Assessed by nurse or physiotherapist; successful if the patient can walk with tolerable pain
Pain and PONV		
Evaluate the effect of SA vs. GA on pain and PONV during early, intermediate, late and long‐term recovery	Rated pain	NRS for pain at rest and mobilisation during early and intermediate recovery and as items 11 and 12 of QoR‐15, POD 1–35
	Use of analgesics (opioids converted to oral morphine equivalents, OME)	Registered by nurse for early and intermediate recovery and reported by the patient after discharge
	Postoperative nausea and vomiting (PONV)	Registered by nurse during early and intermediate recovery and as an item in QoR‐15, POD 1–35
	Patient‐reported outcomes of surgical intervention	HOOS or KOOS at 4 weeks, 6 and 12 months postoperatively
Safety (additional)		
	Incidence of predefined adverse outcomes (specified in the full trial protocol)	Collected from start of anaesthesia to end of follow‐up 2 by patient or study staff
	Need of blood transfusion	Blood transfusion recorded in medical records
Surgical outcomes		
Evaluate the effect of SA vs. GA on intraoperative parameters	Duration of surgery	Intraoperatively recorded data on start and end of surgery
	Intraoperative blood loss	Data from anaesthesia records

*Note:* Outcomes shown in italics are the five key secondary outcomes; all remaining outcomes are exploratory.

Abbreviations: AE, adverse event; AxMP, auxiliary medicinal product; EQ‐5D‐5L, European Quality of Life 5 Dimensions 5 Level version; GA, general anaesthesia; HOOS, Hip disability and Osteoarthritis Outcome Score; KOOS, Knee injury and Osteoarthritis Outcome Score; NRS, Numeric Rating Scale; OME, oral morphine equivalents; PACU, post‐anaesthesia care unit; POD, postoperative day; PONV, postoperative nausea and vomiting; QALY, quality‐adjusted life year; QoR‐15, Quality of Recovery‐15; SA, spinal anaesthesia; SAE, serious adverse event; THA, total hip arthroplasty; TKA, total knee arthroplasty.

**TABLE 3 aas70283-tbl-0003:** PACU discharge criteria and indicators of possible discharge from hospital.

**PACU discharge criteria**	
Respiration	SpO2 ≥ 93% with < 4 L O2
Circulation	BP 80%–120% of preoperative values HR 45–100/min
Temperature	≥ 36°C, 0°C
Activity	Ability to move feet if SA
Pain	NRS ≤ 4
**Indicators of possible discharge from hospital**	
Pain	NRS ≤ 4 at rest
Ambulation	Able to walk with tolerable pain Able to walk one flight of stairs (if present at home)
Surgical dressings	No signs of active bleeding
Labs	Hb ≥ 100 g/L
Voiding	Normal
Radiological examination of prosthesis	Performed

Key and exploratory secondary outcomes are listed in Table 2.

### Schedule of Assessments

2.11

See Table 4.

**TABLE 4 aas70283-tbl-0004:** Summary of the main data collection time points and instruments.

Measurements and activities	Timepoint
Assessment of inclusion and exclusion criteria	Screening
Informed consent	
Patient characteristics	
Medical history	
Opioid use	
Type of surgery (planned)	
Pregnancy test (if applicable)	
Assessment of inclusion and exclusion criteria	
EQ‐5D‐5L, HOOS/KOOS	Baseline
QoR‐15	
Productivity	
Randomisation	Preoperative care and anaesthesia
Administered drugs (AxMP, concomitant medications)	
Needle used, spinal medications and dosage (SA group)	
TIVA protocol used	
Time for start of anaesthesia	
Time of initiation and completion of sterile draping and skin disinfection	
Staff present during anaesthesia induction	
Predefined adverse outcomes	
AEs/SAEs	
Time for start of surgery	Intraoperative (surgery) Day 0
Surgical method	
Bleeding	
Dose of Propofol and remifentanil	
Dose of systemic and local tranexamic acid	
Administered drugs (AxMP, concomitant medications)	
Airway management	
Anaesthesia staff present during surgery	
Time for end of surgery	
Predefined adverse outcomes	
AEs/SAEs	
*Follow‐up 1*	
Pain levels (NRS)	Immediately postoperative (early recovery)
Administered drugs (AxMP, concomitant medications)	
Predefined adverse outcomes	
AEs/SAEs	
Pain levels (NRS) at 1 h after surgery and highest during the first postoperative hour	First postoperative hour (early recovery)
Administered drugs (AxMP, concomitant medications)	
PONV	
Dizziness	
Predefined adverse outcomes	
AEs/SAEs	
PACU discharge criteria (Criteria specified in full in the trial protocol)	Discharge from PACU to the ward
Pain levels (NRS) at discharge and highest during this phase	
Time of discharge	
Administered drugs (AxMP, concomitant medications)	
Analgesics use	
Predefined adverse outcomes	
AEs/SAEs	
The time of first mobilisation	Intermediate recovery (Ward)
Transfusions (number of units transfused)	
Deviations from routine care at site, as described in protocol	
The time when patient fulfils indicators for end of phase III, intermediate recovery (Criteria specified in full in the trial protocol)	
Administered drugs (AxMP, concomitant medications)	
Analgesics use	
Predefined adverse outcomes	
AEs/SAEs	
Time of discharge from hospital.	At discharge from hospital
Predefined adverse outcomes	
AEs/SAEs	
*Follow‐up 2—Conducted both in discharged and non‐discharged patients*	
QoR‐15, Analgesics use	POD 1–14 (daily)
Patient reported predefined adverse outcomes (Specified in full in the trial protocol)	
AEs/SAEs up to POD 3	
Predefined adverse outcomes	
Readmission monitoring	
QoR‐15, Analgesics use	POD 15–35 (weekly ±2 days)
Patient reported predefined adverse outcomes (Specified in full in the trial protocol)	
Semi‐structured interviews (14–60 days postoperatively)	
AEs/SAEs	
Predefined adverse outcomes	
Readmission monitoring	
EQ‐5D‐5L, HOOS/KOOS, Productivity questionnaire	4 weeks postoperative (±7 days)
Healthcare consumption data	
AEs/SAEs	
Predefined adverse outcomes	
Readmission monitoring	
*Follow‐up 3*	
EQ‐5D‐5L, HOOS/KOOS, Productivity questionnaire	6 months postoperative (±14 days)
Prescription and healthcare consumption data	
*Follow‐up 4*	
EQ‐5D‐5L, HOOS/KOOS, Productivity questionnaire	12 months postoperative (±14 days)
Prescription and healthcare consumption data	

Abbreviations: AE, adverse event; AxMP, auxiliary medicinal product; EQ‐5D‐5L, European Quality of Life 5 Dimensions 5 Level version; HOOS, Hip disability and Osteoarthritis Outcome Score; KOOS, Knee injury and Osteoarthritis Outcome Score; NRS, Numeric Rating Scale; PACU, post‐anaesthesia care unit; POD, postoperative day; PONV, postoperative nausea and vomiting; QoR‐15, Quality of Recovery‐15; SA, spinal anaesthesia; SAE, serious adverse event; TIVA, total intravenous anaesthesia.

### Sample Size

2.12

The trial will enrol 600 participants (300 per group). This sample size provides 80% power at a two‐sided 5% significance level to detect an absolute difference of 10 percentage points in successful same‐day discharge between groups, with expected success rates of 70% (GA) and 80% (SA). To account for potential loss to follow‐up, the sample size allows for approximately 1% attrition (*n* = 6 participants). The effect size was informed by prior literature, retrospective cohort data and clinical consensus [21].

### Data Collection and Management

2.13

Trial data will be captured in an electronic case report form. Data quality will be supported by built‐in checks, monitoring and source data verification according to risk‐based monitoring principles. Data will be pseudonymised using a trial‐specific code; the re‐identification key will be stored locally at each site. All data handling will comply with the General Data Protection Regulation (GDPR) and applicable Swedish data protection legislation.

### Statistical Analysis

2.14

Analyses will follow the intention‐to‐treat principle. The primary analysis of the primary outcome will compare the proportion of successful same‐day discharge between groups using a chi‐square test (or Fisher's exact test if appropriate). A prespecified adjusted analysis using logistic regression including treatment group, type of surgery and study site as fixed effects will also be performed, consistent with the stratified randomisation; both analyses will be reported. Effect estimates will be reported as risk difference and odds ratio with 95% confidence intervals. Analyses adjusted for other prespecified baseline variables will be performed as appropriate. The full analytical approach is prespecified in the statistical analysis plan, which will be finalised prior to database lock.

Continuous secondary outcomes will be analysed using independent *t*‐tests or non‐parametric alternatives as appropriate, and regression models for adjusted analyses. Repeated‐measures outcomes (e.g., QoR‐15 trajectories) will be analysed using mixed‐effects models including treatment group, time and group‐by‐time interaction, with participant‐level random effects and, where appropriate, site‐level effects. Binary safety endpoints will be analysed using chi‐square/Fisher's exact tests and logistic regression. Time‐to‐event endpoints may be analysed using Kaplan–Meier methods and Cox models where appropriate. A two‐sided significance level of 0.05 will be employed.

An interim analysis of the primary outcome is planned after approximately 300 participants have completed primary endpoint assessment to allow early stopping for both futility and safety. A group sequential design with O'Brien‐Fleming boundaries will be used to preserve the overall two‐sided type I error at 0.05. Exact stopping boundaries will be based on the observed information fraction at the interim analysis.

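### The primary chi-square test leaves out the site and procedure strata used to randomise; if those strata predict discharge, it is mildly conservative and gives up some precision

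*Protocol article*

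**What the plan says.** Protocol article, section 2.7 (Randomisation and Allocation Concealment) describes 1:1 permuted-block allocation with "stratification by site and procedure (THA/TKA) to balance allocation over time". Section 2.3 (Study Design) names the same two factors.

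Section 2.14 (Statistical Analysis) then fixes the primary analysis of the primary outcome as a comparison of proportions "between groups using a chi‐square test", with Fisher's exact test as the fallback. Neither test uses the strata. The section goes on to say that a logistic regression including "treatment group, type of surgery and study site as fixed effects will also be performed", describes this model as matching the stratified randomisation, and commits to reporting both analyses. Effects are to be given as a risk difference and an odds ratio, each with a 95% interval.

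Section 2.12 (Sample Size) plans 300 participants per arm for "80% power at a two‐sided 5% significance level" with 70% (GA) against 80% (SA), and adds that "the sample size allows for approximately 1% attrition". This is a calculation for two simple proportions, so it matches the unstratified test.

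**The concern.** Permuted blocks within strata make the arms nearly equal in their mix of sites and procedures. Differences in discharge rate between strata therefore contribute almost nothing to the chance variation of the treatment difference. The chi-square variance is computed from the pooled success rate and still contains that between-stratum variation. Where the strata are prognostic, the standard error is too large, the unadjusted interval too wide, and the true type I error below the nominal 5%.

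What is at stake is efficiency. The trial takes the trouble to stratify, and its Discussion gives site-level variation in co-interventions as a reason for doing so. It then bases its main decision on the one of its two planned analyses that does not use the strata. Section 5.3 says that same-day discharge rates vary widely, section 2.9.3 allows sites to differ in agents and doses, and section 5.1 concedes some subjectivity in the discharge decision. A prognostic effect of site is therefore plausible, though not quantified.

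**Working it through.** **Step 1: reproduce the plan's sample size.** Inputs from section 2.12: p1 = 0.70, p2 = 0.80, two-sided alpha 0.05, power 80%, attrition about 1%. With the pooled rate 0.75:

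n per arm = [1.960 × √(2 × 0.75 × 0.25) + 0.842 × √(0.70 × 0.30 + 0.80 × 0.20)]² / 0.10²
= [1.960 × 0.6124 + 0.842 × 0.6083]² / 0.01 = (1.200 + 0.512)² / 0.01 ≈ 293.2, so 294.

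Total 588; 588 / 0.99 = 594 after attrition, against 600 planned. Power of the unstratified test is 80.9% at 300 per arm and 80.5% at 297 per arm. The plan's figure reproduces.

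**Step 2: size of the standard-error excess.** With balanced strata of equal size, the ratio of the chi-square standard error to the correct one is

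ratio = √[ p̄(1 − p̄) / mean of p_s(1 − p_s) ],

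where p_s is the success rate in stratum s and p̄ the overall rate. The documents give no p_s, so an odds ratio (OR) for each of site and procedure is assumed. Two sites are named in section 4 (Trial Status), which with two procedures makes four strata.

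Worked example, OR 2 for each factor, overall rate 75% in both arms: stratum rates 61.4%, 76.1%, 76.1%, 86.4%. The values of p_s(1 − p_s) are 0.237, 0.182, 0.182, 0.118, with mean 0.1796. Ratio = √(0.1875 / 0.1796) = 1.022. The true two-sided alpha is then about 2 × [1 − Φ(1.960 × 1.022)] = 2 × [1 − Φ(2.003)] ≈ 0.045.

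**Step 3: simulation.** 400,000 trials per scenario, 75 per arm in each of four strata, exact balance, constant log-odds shift within strata, overall rates 75%/75% (null) or 70%/80% (alternative). Chi-square and Cochran-Mantel-Haenszel (CMH) were both run without continuity correction.

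| OR per factor (assumed) | SE excess (null) | Alpha, chi-square | Alpha, CMH | Power, chi-square | Power, CMH | Power forgone (points) |
|---|---|---|---|---|---|---|
| 1 | 0% | 5.1% | 5.1% | 81.1% | 81.1% | 0 |
| 1.5 | 0.8% | 4.9% | 5.0% | 81.3% | 81.7% | 0.4 |
| 2 | 2.2% | 4.5% | 5.0% | 81.5% | 82.6% | 1.1 |
| 3 | 5.3% | 3.9% | 5.0% | 82.3% | 84.8% | 2.6 |
| 4 | 8.2% | 3.4% | 5.0% | 83.0% | 86.7% | 3.7 |

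The alpha of 5.1% at OR 1 is identical for the two tests, so none of it comes from ignoring the strata. If only site is prognostic, with OR 2, alpha is 4.7% and power 81.4% against 81.9%.

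**Step 4: scale of the assumptions.** Under the null, OR 2 per factor means strata running from 61% to 86%; OR 4 means 48% to 94%. The lower rows of the table therefore need very large differences between strata.

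**The case against.** The strongest reply is that the plan is coherent as it stands. The trial was sized for the unstratified test, the adjusted model is prespecified with exactly the two stratification factors, both results will be reported, and their order is explicit. Sites share eligibility limits and a common perioperative framework, so strong stratum effects may not occur. All of this stands, and it limits the point to which of two planned analyses should be primary.

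A reader might infer more than the documents support:

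- **That power falls short of 80%.** It does not. Chi-square power was at least 81% in every scenario, and it rises slightly as the strata become more prognostic. What is lost is only the extra power that a stratified test would bring. Nor does the thin margin of 80.5% at 297 per arm strengthen the case: that figure takes no account of stratum effects, and without them stratification gains nothing.
- **That the primary test is invalid.** The error is on the conservative side. It does not inflate false positives, and nothing here shows bias in the estimate.
- **That the adjusted analysis can give only an odds ratio.** Section 2.14 promises a risk difference as well as an odds ratio. How the adjusted risk difference is obtained can properly be left to the SAP, which is not shown.
- **That fixed site effects will become sparse.** Section 4 says only that sites may be added. Sparse cells would in any case affect a site-by-procedure stratification more than the planned additive model, so this is no argument for the change.

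**Conclusion.** The point holds conditionally and is modest. The test labelled primary does not use the factors by which the trial randomises. If site or procedure predicts same-day discharge, that test is conservative and forgoes precision: about 0.4 to 1 point of power for odds ratios of 1.5 to 2 per factor, and about 2.5 to 4 points for odds ratios of 3 to 4. If neither factor is prognostic, nothing is lost.

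The direction is certain; the size is assumed, because the documents give no rates by stratum. The figures also assume four equal strata, exact balance within strata, no attrition and no interim look, with CMH standing in for the planned logistic model. More sites with differing discharge rates would enlarge the effect. The stated power is met and a positive finding would be sound, so this is an improvement in efficiency and calibration and not the repair of an error.

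**What to change.** In section 2.14 and in the SAP, make the analysis adjusted for site and procedure primary. Either of two forms will do:

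- a CMH test stratified by site and procedure, with the Mantel-Haenszel risk difference and its 95% confidence interval; or
- the logistic model already planned, with a standardised risk difference and its 95% confidence interval.

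Name one of them. Use the same statistic at the interim analysis, so that the O'Brien-Fleming boundary is applied to the test that will decide the trial. Keep the unadjusted chi-square as a supportive analysis.

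The cost is a sentence or two in each document. It needs no additional participants or data and no change to the sample size. The trial was not yet recruiting when the article was submitted; a change made before outcome data are seen cannot be read as data-driven.
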